## Methods/Design

The proposed research regards a multicentre open label randomized controlled trial in women with GDM between 38+0 and 39+0 gestational weeks. The study will be carried out by the GINEXMAL Study Cooperative Research Group including 9 Teaching Hospitals, 5 in Italy and 4 abroad. The Institute for Maternal and Child Health - IRCCS Burlo Garofolo (Italy) together with The Helen Schneider's Hospital for Women - Rabin Medical Centre (Israel) will be the coordinating centre of the research project.

A total sample of 1760 patients (N = 880 per intervention group) will be recruited. The sample size has been estimated to be sufficiently large to achieve significant results with concerns to the main outcome of the study. In particular, it will be able to demonstrate a difference between the two arms ≥ 6% (31% of C-section in the expectant group and 25% in the induction group; relative difference between the 2 groups equal to 20% in favour of induction [13]), considering α error equal to 5% and 80% power.

Randomization will be centralized and coordinated by the Epidemiology and Biostatistics Unit (IRCCS Burlo Garofolo, Italy) using a computer-based method. The randomization list will be blocked (using blocks with a size of 10) and stratified by centre. The allocation concealment will be guaranteed through the use of closed opaque envelopes, consecutively numbered. In each envelope a patient's allocation group will be indicated, based on randomization. The study will be an open label trial because of the practical impossibility to blind either health professionals or patients to the allocation group.

Medical personnel directly involved in the management of the patient, will open the first available envelope and assign the patient to the corresponding randomization group (experimental group: induction of labour or control group: expectant management). The recruitment phase of the study will last 2 years.

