**Figure 1 F1:**
[figure not shown]
**Trial Flow chart**.

Patients enrolled in the conservative management arm will be followed up twice weekly by Electronic Fetal Heart Rate monitoring and Biophysical profile (Figure 1). Patients will be followed up until 41+0 gestational weeks. Women, who will not deliver by this gestational age, will be admitted for labour induction (see the protocol above). Induction of labour will be offered when non-reassuring fetal status is suspected. All patients in the conservative arm will undergo fetal weight ultrasound estimation prior to induction. Patients with estimated fetal weight over 4000 gr will be offered a caesarean section.

General information on recruited patients, outcomes and randomization group will be indicated in an appropriate paper questionnaire in the first instance and then reported on an electronic database accessible from different study sites in the second instance. In each participating centre, medical personnel will fill up the electronic form directly. Data will be kept anonymous and will be analyzed by the Epidemiology and Biostatistics Unit - IRCCS Burlo Garofolo, using STATA 9 statistical package. Continuous variables will be reported as mean and standard deviation, categorical variables as proportions and percentages. The two groups will be compared by their main characteristics to evaluate the efficacy of the randomization process. To evaluate the main outcome of the study, C-section incidence will be compared between the two groups using the χ^2 ^test. Possible confounders such as: blood glucose control, obesity, participating centre policy etc. will be controlled through multivariate analysis (logistic regression). To compare secondary outcome variables between the two groups, the ANOVA technique will be used for continuous variables and χ^2 ^test for categorical. Statistically significant differences will be determined by a p-value inferior to 0.05. Although crossovers between the two allocation groups could complicate data interpretation, it is impossible to prevent them. However, data will be analysed by intention-to-treat. Finally, a sensitivity analysis will be carried out to confirm that results do not change significantly despite the variety of populations included in the study.

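### The planned sensitivity analysis takes absence of a significant change as confirmation that results are consistent across populations, which the trial is not sized to show

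*Protocol article*

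**What the plan says.** The analysis paragraph of the protocol article (Methods/Design, after Figure 1) ends with the statement that "a sensitivity analysis will be carried out to confirm that results do not change significantly despite the variety of populations included in the study". A few lines earlier the same paragraph gives its only definition of significance: "Statistically significant differences will be determined by a p-value inferior to 0.05".

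The populations are not defined. The opening of Methods/Design describes a study group "including 9 Teaching Hospitals, 5 in Italy and 4 abroad", and randomization is "stratified by centre". The sample size rests on the overall comparison alone: "31% of C-section in the expectant group and 25% in the induction group", "considering α error equal to 5% and 80% power", giving 880 women per arm. The article states no margin, interval or size of difference at which results would count as changed.

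**The concern.** The sentence fixes two things: the aim, which is to confirm sameness, and the criterion, which is that no significant change is seen. Failing to detect a difference does not show that there is none. Such a criterion also rewards imprecision, since the fewer women there are per population, the more readily consistency is declared.

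Real differences in effect are plausible in this trial. When prostaglandin ripening fails, Methods/Design leaves the next step to each site's practice, and one of the options is C-section, the primary outcome. The protocol also lists centre policy among possible confounders. Adjusting for it in the logistic model handles differences in baseline risk but does not address whether the effect of induction differs between centres. At stake is a statement that the C-section result holds across a varied set of hospitals when the data could not settle the matter.

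**Working it through.** **Inputs from the protocol (Methods/Design).** C-section risk 31% (expectant) and 25% (induction); 880 women per arm; alpha 5%; power 80%; nine hospitals, five in Italy and four abroad.

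**Assumptions, because the protocol gives no figures.** The populations are two regions. Recruitment per centre is equal, so the split is 5:4. The comparison is a two-sided 5% test of the difference between the two regional risk differences.

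**1. The protocol's own sample size.** With pooled variance, two-sided 5% and 80% power:

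n = [1.96·√(2·0.28·0.72) + 0.8416·√(0.31·0.69 + 0.25·0.75)]² / 0.06² = 878 per arm.

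Power with 880 per arm is 80.1%. The stated figure reproduces, and it is used up by the overall 6-point contrast.

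**2. Precision of a between-region comparison.** Women per arm: 880·5/9 = 489 and 880·4/9 = 391. At the planning rates the variance of one regional risk difference is (0.31·0.69 + 0.25·0.75)/n = 0.4014/n. Hence

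SE = √(0.4014/489 + 0.4014/391) = 0.0430, or 4.3 points.

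The 95% interval for the difference in effects is ±1.96·4.30 = ±8.4 points.

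**3. Power for an illustrative difference.** Take true effects of -9 and -3 points (simple mean -6), a difference of 6 points. Then 6/4.30 = 1.40, and power = Φ(1.40 - 1.96), about 29%. Simulation with 200,000 runs gives 29% on the risk-difference scale and 32% on the log-odds-ratio scale. In this scenario about 7 trials in 10 would show no significant change.

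**4. Difference needed for 80% power.** (1.96 + 0.84)·4.3 = about 12 points, twice the planned overall effect.

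**5. Range over the unknown split.** Here the two effects are kept in a 3:1 ratio and their patient-weighted mean at 6 points, so the individual effects shift with the split. The control risk is 31% in both regions.

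| Split | Power, larger effect in larger region | Power, larger effect in smaller region |
|---|---|---|
| 50:50 | 29-32% | 29-32% |
| 5:4 | 26-29% | 32-35% |
| 70:30 | 19-21% | 38-42% |
| 80:20 | 14-15% | 39-43% |
| 90:10 | 9-10% | 32-35% |

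In each cell the lower figure is for the risk-difference scale and the higher for the log-odds-ratio scale. Power stays below one half throughout.

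**6. Centres instead of regions.** If nine equal centres (98 women per arm each) are compared by a Cochran Q test on 8 degrees of freedom, with five centres at 9 points and four at 3 points, simulated power is 14%.

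**The case against.** The strongest objection is that the protocol names no interaction test. A sensitivity analysis ordinarily means repeating the main analysis with some populations removed or varied and seeing whether the conclusion stands. The word for significance may be loose: the p < 0.05 threshold follows sentences about comparing the two arms, and the Discussion uses the same adverb in an everyday sense when it says GDM affects fetal growth. The populations could be centres, obesity or glucose-control groups, or women diagnosed under different criteria. Italy versus abroad is one choice among several. The details may sit in a full protocol or SAP that is not shown.

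Much of this stands. A reader might infer that the protocol commits to a test that would wrongly confirm consistency in about 71% of trials. The documents do not support that: the test, scale, populations and split are all assumed, and so is the -9 versus -3 scenario. Nor should a threefold difference be read as a threefold ratio of odds ratios, which would almost always be detected (log 3 / 0.214 = about 5 standard errors). And no passage says that the authors will announce consistency across all centres.

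What does not fall is the stated logic. The complaint is not about missing detail. The article does say what the analysis is for and what counts as success, and an SAP that followed the sentence faithfully would inherit the flaw. The exclusion reading does not rescue it. With nine equal centres, dropping one whose effect differs from the rest by 6 points moves the overall estimate by only 6/9 = 0.67 points, so little visible change is expected even when one centre differs substantially.

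**Conclusion.** The point holds as a cheap improvement to a secondary analysis. On its plain reading, the sentence accepts a non-significant change as confirmation of consistency, and a trial sized for a 6-point overall effect cannot supply that confirmation. The sizes given are illustrations, not a demonstrated failure rate of a specified procedure. The ±8.4-point interval depends less on the scenario than the power figures do, but it still assumes two regions, a near-even split and the planning rates. A more uneven split widens it, to about ±14 points at 90:10 (1.96·7.1). A true overall effect well above 6 points could leave more room to detect differences. Nothing here touches the primary χ² test, the sample size or the conduct of the trial.

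**What to change.** Replace the sentence with a plan to estimate:

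- Estimate the C-section difference by centre, which is already the stratification factor, and by Italy versus abroad if wanted.
- Fit a treatment-by-centre term (interaction or random effect) or a treatment-by-region interaction in the logistic model, and report it with its 95% confidence interval.
- State that consistency will be claimed only as far as that interval allows, and that a non-significant interaction will not be taken as confirmation.

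The cost is one extra model and a changed sentence, with no new data and no change to the sample size. The drawback is that, with an interval of about ±8.4 points or wider, the trial will probably be unable to claim confirmed consistency.

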## Discussion

The aim of the present study is to assess whether induction of labour at term would reduce C-section rate and ameliorate maternal and neonatal outcomes when compared to expectant management in pregnancies affected by GDM.

The main outcome of the study was planned to be a composite of main neonatal morbidity and mortality outcomes possibly related to GDM. The choice of creating a composite outcome derived from the practical impossibility of using shoulder dystocia alone as a single outcome. The rarity of this event would have precluded the possibility of carrying out the study, which would require a very large number of women to obtain significant results. The necessity of including very rare endpoints in a composite outcome in obstetrics research has been recently highlighted [23]. The attempt to include in a unique composite, the neonatal outcomes of interest, has unfortunately failed. In fact this process would have required combining very serious events, such neonatal death or shoulder dystocia, to neonatal hypoglycaemia or hyperbilirubinemia related to much less serious consequences, and for this reason unfeasible.

Therefore the main outcome of the study was decided to be the incidence of C-section among women undergoing induction of labour and those who will be assigned to expectant management with attentive maternal and fetal monitoring. This is a very relevant outcome both for women's health and for health service organizations. Furthermore, C-section rate was the main outcome of the only randomized controlled trial previously carried out on this topic [13].

Secondary outcomes of the study will be assessed at time of delivery and/or during maternal and neonatal admission until discharge. Outcomes evaluated at delivery are: gestational age, mode of delivery (spontaneous or operative vaginal delivery, C-section), spontaneous or instrumental third stage of labour, presence of perineal tears or performance of an episiotomy, postpartum haemorrhage (defined as bleeding from the genital tract of 1000 ml or more in the first 24 hours following the delivery of the baby) [20]. Furthermore, the occurrence of shoulder dystocia, defined as a delivery that requires additional obstetric manoeuvres to release the shoulders after gentle downward traction has failed, will be evaluated [24]. Shoulder dystocia occurs when either the anterior or, less commonly, the posterior fetal shoulder impacts on the maternal symphysis or sacral promontory [24] and its diagnosis will be confirmed by an apposite committee for serious adverse events. Serious adverse outcomes such as shoulder dystocia, fourth-degree perineal tears and uterine rupture will be reported to an independent data monitoring committee. Finally, the eventual manoeuvres performed to disengage the shoulder, newborn's birth weight, Apgar score at 1', 5' and 10' minutes, occurrence of arterial cord pH inferior to 7.02 will be recorded and evaluated.

The remaining secondary outcomes will be assessed until maternal and fetal discharge and are as follows: need for blood transfusion (whose main determinant should be the clinical picture and whose main therapeutic goals are to maintain haemoglobin > 8 g/dl, platelet count > 75 × 109/l, prothrombin < 1.5 × mean control, activated prothrombin times < 1.5 × mean control, fibrinogen > 1.0 g/l, when used in the most appropriate combination of intravenous clear fluids and blood products) [25], maternal or neonatal intensive care unit admission, duration and diagnosis, neonatal birth trauma (Erb's palsy, bone fracture, intra-cerebral/intra-ventricular haemorrhage, subdural hematoma), neonatal respiratory distress/transient tachypnea, neonatal need for respiratory support, neonatal hyperbilirubinemia, polycythemia or hypoglycaemia and maternal and perinatal death.

Analysis of neonatal plasma glucose level collected 1-2 h after delivery is performed at the local laboratory and results are provided to caregivers. Additional measurements of plasma glucose may be performed for clinical indications at the discretion of the attending physician, if signs or symptoms suggest sustained or later development of hypoglycemia. The need for other clinical assessments, such as bilirubin levels or neonatal respiratory function, is determined by specific clinical indications. All data regarding the assessment of potential neonatal morbidities are collected from the medical records of the newborn.

GDM is a common complication of pregnancy and could significantly affect fetal growth. Strong evidence supporting a specific management on timing of delivery of pregnant women with GDM is missing and there is no consensus on this matter. Expectant monitoring could determine an increase in macrosomic fetuses' incidence, leading to a higher C-section rate. Although induction of labour could prevent fetal macrosomia and its consequences, its performance is thought to be possibly related to an enhancement in C-section and instrumental vaginal delivery rates [26]. The aim of the present trial is to provide evidence on the best management of women at term, previously diagnosed with GDM, in terms of maternal and neonatal outcomes.

The GINEXMAL protocol and copies of all forms may be found on the following website: http://www.burlo.trieste.it. Additional file 1 - Patient information sheet and consent form, Additional file 2 - Patient recruitment form.

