**Exclusion Criteria**

Pre-GDM
Prior C-section
Suspected estimated foetal weight > 4000 g at enrolment
Any known contraindications to vaginal delivery
Uncertain gestational age
Non reassuring foetal wellbeing necessitating delivery
Maternal pregnancy-related disease necessitating delivery
Bishop score > 7 at enrolment
Known foetal anomaly

If there are no other contraindications to deliver vaginally, patients will be enrolled between 38+0 and 39+0 weeks of gestational age (verified by last menstrual period (LMP) and confirmed by first trimester ultrasound). In the case of a discrepancy, gestational age assessed by ultrasound in the first trimester will be considered as the true reference. Uncertain gestational age or any major fetal anomaly will cause exclusion from the trial (Table 1). Women diagnosed with pre-gestational diabetes or demonstrating a prior C-section in their obstetrical history will be excluded. The identification of non-reassuring fetal status assessed by cardiotocography alone or as a formal part of a biophysical profile [22] or the presence of maternal or fetal conditions complicating pregnancy (e.g. severe preeclampsia/HELLP Syndrome or severe fetal growth restriction) and requiring immediate obstetrical intervention (prompt delivery or prompt C-section) will lead to the patient's exclusion.

After careful evaluation of inclusion and exclusion criteria (Table 1), suitable patients will have been identified. On the day of enrolment, an ultrasound assessment of fetal weight, as well as a Bishop score evaluation, will be performed. Whenever the estimated fetal weight exceeds 4000 gr, patients will be excluded from the trial and offered a C-section. A Bishop score greater than 7 will automatically exclude the patient from the trial. Furthermore, an attentive evaluation of possible contraindications to vaginal delivery and an assessment of fetal wellbeing through a cardiotocographic trace will be carried out at enrolment. The remaining inclusion/exclusion criteria will be assessed through the evaluation of the patient's current and past obstetric records.

Eligible women will be provided a comprehensive explanation of the project by the obstetrician on call, in terms of study procedures and risks versus benefits attached. Patients wishing to take part will be asked to sign a written consent form before being allocated to the randomization group.

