Data about obstetric history will be collected through consultation with the patient and evaluation of the patient's previous records and clinical reports. The outcomes will be evaluated during delivery and until maternal and neonatal discharge. Perinatal and maternal deaths will be identified until discharge. Perinatal deaths should include events up to 7 days after birth and most newborns will be discharged earlier. Our assumption is that perinatal death would occur almost exclusively in newborns manifesting complications during admission and consequently this could be accurately estimated by the time of discharge. At enrolment, patients assigned to the induction group will be admitted to the obstetric ward (Figure 1). Induction of labour will be performed by using dinoprostone, 2 mg vaginally, or dinoprostone, 0.5 mg intracervically, in 6-8 hour intervals (up to 5 doses) or dinoprostone, 10 mg vaginal device. Once the patient's Bishop score exceeds 7 or regular contractions are diagnosed, patients will be transferred to the delivery ward for artificial rupture of membranes (ARM) or oxytocin augmentation as indicated. Patients, in which cervical ripening does not occur (Bishop score < 7) after 5 attempts with Prostaglandin E2 (PGE2), will be offered either oxytocin or Foley catheter induction or C-section, according to local protocols.

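### Outcome assessment is worded as starting at delivery, so non-fatal antenatal harms, which arise almost only in the expectant arm, are not outcomes, and stillbirth is not named

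*Protocol article*

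**What the plan says.** Two places in the protocol article set the time of outcome assessment. Methods/Design, after Table 1: "The outcomes will be evaluated during delivery and until maternal and neonatal discharge". Discussion, at the start of the secondary outcomes: "Secondary outcomes of the study will be assessed at time of delivery and/or during maternal and neonatal admission until discharge". The Discussion then divides the secondary outcomes into those taken at delivery and the remaining ones taken up to discharge, and the two lists together read as complete.

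The arms differ in what comes before delivery. Both enter in the same week: "patients will be enrolled between 38+0 and 39+0 weeks of gestational age". For induction, "At enrolment, patients assigned to the induction group will be admitted to the obstetric ward". Expectant-arm women go home (Abstract) and are "followed up twice weekly by Electronic Fetal Heart Rate monitoring and Biophysical profile". Their wait has an upper limit: "Patients will be followed up until 41+0 gestational weeks".

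On deaths, Methods/Design says "Perinatal and maternal deaths will be identified until discharge". It supports ascertainment at discharge with the assumption that "perinatal death would occur almost exclusively in newborns manifesting complications during admission". The Discussion lists maternal and perinatal death as secondary outcomes. Serious adverse events go to a committee (Methods/Design), and the three examples in the Discussion (uterine rupture, shoulder dystocia and fourth-degree tears) are all events of delivery.

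**The concern.** The trial compares delivering now with continuing the pregnancy under surveillance. The time between randomisation and delivery is therefore part of the strategy under test, and only one arm has a material amount of it. An outcome list that begins at delivery captures the complications of induction, which occur in hospital, but has no entry for a non-fatal complication of waiting that resolves or is treated before the birth.

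The protocol itself treats such conditions as important. Severe pre-eclampsia and non-reassuring fetal status lead to exclusion at enrolment, and suspected non-reassuring status later leads to an offer of induction in the expectant arm. Yet neither condition, when it arises after randomisation, is an outcome. The secondary objective is to compare maternal and neonatal outcomes between the arms, and on the maternal side that comparison would miss one kind of harm in one arm.

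**Working it through.** **The plan's own figure.** The sample size rests on the primary outcome and does not depend on this point. With p1 = 0.31, p2 = 0.25, mean 0.28, two-sided 5% and 80% power (the article does not state sidedness):

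n = [1.960·√(2·0.28·0.72) + 0.842·√(0.31·0.69 + 0.25·0.75)]² / 0.06² = [1.2445 + 0.5332]² / 0.0036 ≈ 878 per arm.

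The plan states 880, for which power is 80.1%. The figure reproduces.

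**Length of the interval.** The limits are 38+0 to 39+0 for enrolment and 41+0 for the end of expectant follow-up (Methods/Design).
- Randomised at 38+0: (41 − 38) × 7 = 21 days at most.
- Randomised at 39+0: (41 − 39) × 7 = 14 days at most.
- Women who deliver sooner have less.
- Induction arm: admitted at enrolment, so almost none.

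**What the lists catch when something goes wrong in that interval.**

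| Event after randomisation, before delivery | Counted as an outcome? |
|---|---|
| Deterioration ending in C-section, low cord pH or Apgar score, or intensive care | Yes, in the randomised arm |
| Further fetal growth | Yes, through birth weight, shoulder dystocia, birth trauma and C-section |
| Maternal death | Yes; an end is stated, no start |
| Fetal death before labour | Probably, as perinatal death, but not stated |
| New pre-eclampsia or gestational hypertension without a listed complication | No |
| Antenatal admission, or delivery prompted by non-reassuring monitoring | No; only gestational age and mode of delivery are recorded, not the reason |

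On the fourth row, stillbirth is named nowhere. The only reasoning given about perinatal death concerns newborns who show complications during admission, and that cannot describe a fetus that dies while the mother is at home.

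**Size.** The documents give no rate for the events in the last two rows, so no bias can be calculated. As an illustration with assumed rates, 880 × p gives:
- 0.1%: 0.9 women
- 0.5%: 4.4 women
- 1%: 8.8 women
- 2%: 17.6 women
- 5%: 44 women

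These are counts of expectant-arm women whose event would not be tabulated. They are not estimates of what will happen.

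**The case against.** A reader might infer that all harm during the wait falls outside the comparison and that the trial will make expectant management look safer than it is. The documents do not support that, for these reasons.

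- **Assessment time is not the period at risk.** The two sentences say when outcomes are evaluated, not that earlier causes are disregarded. With intention-to-treat analysis, the consequences that show at or after delivery are credited to the randomised arm.
- **The hazard that the protocol stresses is captured.** Background and Discussion describe the risk of waiting as macrosomia and a resulting rise in C-section. Both are recorded, and C-section is the primary outcome.
- **Deaths are listed without a start.** Perinatal death ordinarily includes late fetal death. The sentence about newborns defends the choice of discharge as the end point and was not written to define when counting begins.
- **Serious adverse event reporting is open.** It has no stated start, and the three events named are only examples.
- **The article is a condensation.** It refers to a full protocol and forms that are not shown and may collect these events.

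All of this stands and narrows the point. It does not remove it. The article states both the assessment window and a secondary list that reads as complete. No entry on that list is a non-fatal antenatal event, and an open serious-event list does not make such an event a compared outcome. Stillbirth needs only an explicit statement. For hypertensive disease something is actually missing.

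One objection also limits the remedy. Antenatal admission and delivery prompted by monitoring can hardly occur in women admitted at enrolment, so testing them between arms would mostly restate the design.

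**Conclusion.** The point holds in a limited form. As worded, assessment runs from delivery to discharge, and no non-fatal antenatal event is a secondary outcome, although only the expectant arm has a material interval (at most 14 to 21 days) in which one can arise. Fetal death before labour is probably covered but is not stated to be.

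Any resulting omission works in one direction, in favour of expectant management. Its size is not determined by the documents, and a claim that the safety comparison will be materially biased would go beyond them. The conclusion assumes that the article's outcome list is the operative one; if the full protocol or forms already collect these events as outcomes, only the article's wording needs correction. The primary comparison and the sample size are unaffected. The change is worth making because the secondary objective is this very comparison and the remedy is cheap.

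**What to change.** 1. State that secondary outcomes and serious adverse events are counted from randomisation to discharge in both arms.
2. State that perinatal death includes fetal death before labour, and report it separately from intrapartum and neonatal death.
3. Add new pre-eclampsia or gestational hypertension after randomisation as a secondary outcome in both arms. Record hypertensive status at enrolment so that new can be judged, because the exclusion covers only disease that requires delivery.
4. Name antepartum fetal death and severe antenatal maternal events among those sent to the adverse event committee.
5. Report antenatal admission and delivery prompted by non-reassuring monitoring descriptively, without a between-arm test.

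The cost is a few more fields on the existing forms. Expectant-arm women are already seen twice weekly, and the Abstract describes that monitoring as maternal as well as fetal, so no visits or participants are added. One drawback remains: closer surveillance in the expectant arm may detect more mild hypertension. Reporting severe disease separately from mild would let readers judge this.

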## Background

GDM is one of the most common complications of pregnancy and its incidence is estimated at 7% [1]. Among women affected by GDM, an increased rate of C-section has been observed, mostly unjustified [2,3]. Recent studies identified a C-section rate among women with this condition as high as 35% [4], and indicated a probability of undertaking a C-section in this group around 1.5 times the probability among non-GDM women [5].

Furthermore, babies born from women with GDM are significantly more exposed to perinatal risk, mostly related to fetal macrosomia [6]. This clinical condition is in fact associated to an increased risk of intrapartum traumatic lesions and asphyxia [7]. The incidence of macrosomia or birth weight above the 90^th ^percentile is more common among these women, in comparison to the general population [8]. These newborns, because of their peculiar intrauterine growth pattern, are characterised by a trunk mass larger than the head and consequently are more exposed to shoulder dystocia, bone fractures and brachial plexus injury, possibly with permanent outcomes [9,10].

The American College of Obstetricians and Gynecologists recommends a caesarean section for women with GDM and estimated fetal weight > 4500 g [11]. The American Diabetes Association recommends that GDM by itself is neither an indication for C-section nor for induction of labour before 38 completed gestational weeks [12]. Pregnancy prolongation beyond 38 weeks increases the risk to develop fetal macrosomia, without reducing C-section rate. As a result, delivery within the 38^th ^week of pregnancy is advisable if there are not other specific obstetric recommendations to determine an alternative management [12].

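### Arterial cord pH is defined only as a value below 7.02, a yes/no event with low power at 880 per arm; the numeric pH should be named and compared alongside the count.

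*Protocol article*

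**What the plan says.** The secondary outcomes are listed in the Discussion of the protocol article. The sentence that covers the newborn's condition at birth names birth weight and the Apgar scores as quantities, but gives cord blood gas only as an event: "occurrence of arterial cord pH inferior to 7.02 will be recorded and evaluated". No expected frequency of that event and no SD of pH appear anywhere.

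The analysis text in Methods/Design (after Figure 1) says that for secondary outcomes "the ANOVA technique will be used for continuous variables", with chi-square for categorical ones, and that "Statistically significant differences will be determined by a p-value inferior to 0.05". As defined, cord pH falls under chi-square.

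The trial is sized on caesarean section alone: "A total sample of 1760 patients (N = 880 per intervention group) will be recruited", for "31% of C-section in the expectant group and 25% in the induction group", "considering α error equal to 5% and 80% power". The Background names asphyxia among the neonatal risks of macrosomia ("associated to an increased risk of intrapartum traumatic lesions and asphyxia").

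**The concern.** Cutting a continuous measurement at a point in its lower tail scores nearly every baby the same way, and most of the information about a difference between arms is lost. The article already has a method for continuous secondary outcomes, but cord pH as defined does not reach it.

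Cord pH is the only biochemical marker of the newborn's condition at birth in the list. In an open-label trial a value read by an instrument is a useful companion to outcomes that depend more on clinical judgement, such as Apgar score or intensive care admission. If the only comparison is a test on a small count, a non-significant result is likely even when a real difference exists, and a reader could take it as reassurance.

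**Working it through.** **1. The plan's own figure.** Inputs from Methods/Design: 31% versus 25%, alpha 5%, power 80%. Sidedness is not stated; two-sided reproduces the figure. The formula is

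n per arm = [1.960·√(2·p̄(1−p̄)) + 0.842·√(p1(1−p1) + p2(1−p2))]² / (p1−p2)², with p̄ = 0.28.

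This gives (1.2445 + 0.5332)² / 0.06² = 3.160 / 0.0036 = 878, against 880 stated. The primary sample size is sound, so 880 per arm is used below.

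**2. The yes/no outcome at 880 per arm.** The rate of pH below 7.02 is an assumption, because the article gives none; 0.3% to 3% is shown. Expected events are 880 × rate. Power for a halving is the exact binomial probability that the uncorrected chi-square test gives p < 0.05. The last two columns use the normal approximation, with the formula in step 1 for the required n.

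| Assumed rate | Events per arm | Power for a halving | n per arm for a halving, 80% power | Increase detectable with 80% power |
|---|---|---|---|---|
| 0.3% | 2.6 | 8% | 15,662 | 5.3-fold |
| 0.5% | 4.4 | 12% | 9,383 | 3.9-fold |
| 1% | 8.8 | 21% | 4,673 | 2.8-fold |
| 2% | 17.6 | 42% | 2,319 | 2.2-fold |
| 3% | 26.4 | 58% | 1,534 | 1.9-fold |

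At the low rates the approximation in the last two columns is rough. For a 20% relative reduction, the size of effect the trial targets for caesarean section, power is about 4% to 12% over the same range (normal approximation).

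**3. What a null count would leave open.** If both arms had a true rate of 1%, the half-width of the 95% interval for the difference would be about 1.96 × √(2 × 0.01 × 0.99 / 880) = 0.0093, or 0.9 percentage points. The interval would be nearly as wide on each side as the rate itself.

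**4. The measured value at 880 per arm.** Detectable mean difference at 80% power, two-sided 5% = SD × √(2/880) × (1.960 + 0.842) = SD × 0.0477 × 2.802 = 0.13 SD. The SD is also an assumption:

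| Assumed SD | All sampled (880 per arm) | Half sampled (440 per arm) |
|---|---|---|
| 0.06 | 0.008 | 0.011 |
| 0.08 | 0.011 | 0.015 |
| 0.10 | 0.013 | 0.019 |

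The second column is there because the article does not say that every baby has a cord sample.

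**The case against.** The strongest reply is that the article names an outcome, not a data field. It says that the full protocol and all forms are on a website, and that neonatal morbidity data come from the newborn's records. The value may well be captured, and further analyses may be planned in documents not shown. That stands as far as data capture goes. A reader might infer that only a tick is kept and that pH could never be rescored; the article does not establish this. What remains is that the outcome, as stated, is the dichotomy.

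Other parts of the reply also stand:

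- That the event will occur in only a few babies per arm is an assumption. It fits rates up to about 1%, not 2% to 3%.
- It would be too strong to say that the outcome will show nothing. Increases of roughly two- to five-fold remain detectable.
- Cord pH is not the only evidence on newborn condition. Apgar scores, respiratory support, intensive care admission and perinatal death are also collected.
- There is no contradiction with the Discussion's remark on shoulder dystocia ("The rarity of this event would have precluded the possibility of carrying out the study"). That explains why it could not serve alone as the main outcome; a rare severe event may still be a secondary one.
- The 7.02 cut-off carries no reference, but nothing in the article contradicts it, so there is no ground for calling it an error.
- A mean difference answers a different question from severe acidaemia. If sampling follows clinical concern, the mean compares groups selected after randomisation.

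The last item limits the fix but does not remove the case for it.

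**Conclusion.** The point holds in a limited form. The stated cord-gas outcome is a dichotomised continuous measurement. At 880 per arm its power for a halving is about 8% to 58% over assumed rates of 0.3% to 3%, below 80% throughout. Compared as values, the same babies would allow a mean difference of about 0.13 SD to be detected, 0.008 to 0.013 pH units for SDs of 0.06 to 0.10. That rests on the assumed SDs and on complete sampling; with half the babies sampled it becomes 0.011 to 0.019.

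A reader might go further and infer that the trial will be uninformative about asphyxia, or that mean pH should replace the threshold. The documents support neither: other neonatal outcomes are collected, large effects on the count can be seen, and severe acidaemia is the more directly clinical question. This is an inexpensive improvement to one secondary outcome, with no bearing on the primary analysis.

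**What to change.** - Name the numeric arterial cord pH as a recorded secondary variable. If the forms already hold it, say so.
- Report the between-arm difference in mean pH with its 95% confidence interval, as a supplement to the count below 7.02.
- Keep that count, and report the difference in proportions with its own confidence interval.
- Report the number of babies sampled in each arm, since selective sampling would weaken both comparisons.
- State that a non-significant difference in the count will not be read as evidence of no difference.

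The cost is at most one numeric field and one further comparison, which the planned method for continuous outcomes already covers. The downside is that a shift in the mean is less directly clinical than severe acidaemia, which is why the two are shown together.
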